#### Serious adverse events

A "serious adverse event" is defined as an event, regardless of the severity of symptoms, that is judged to be serious or not according to the following criteria

1. death
2. Items that may lead to death
3. Those that require hospitalization or extended hospitalization for treatment.
4. obstacle
5. Items that may lead to disability
6. Serious according to 1~5
7. Congenital diseases or anomalies in later generations

### 10.3 Assessment of adverse events

Adverse events observed during the conduct of clinical research will be evaluated according to the schedule specified in "Observation and Examination Items and Schedule".

The severity of adverse events will be determined based on the NCI-Common Terminology Criteria for Adverse Events (NCI-CTC-AE Ver4.0 Japanese version).

### 10.4 Anticipated adverse events and responses

#### 10.4.1 Anticipated adverse events

In a previous study of 24 patients who received activated NK cell therapy to prevent recurrence of hepatocellular carcinoma after living donor liver transplantation, the adverse events that occurred were as follows, all of which were resolved by follow-up or drug administration.

1. Infusion reaction: fever, malaise (3/24 cases, 12.5%), chills, myalgia, diarrhea (2/24 cases, 8.4%), nausea, skin rash, sinus tachycardia (1/24 cases, 4.2%)
2. GVHD (0/24 cases, 0%)
3. Infectious diseases (7/24 cases, 29.2%)
4. Contamination of transplanted cells (including delayed onset of infection in the donor) (0/24 cases, 0%)

#### 10.4.2 Dealing with Adverse Events

1. If necessary, treat with circulatory and respiratory support and steroids.
2. Take necessary measures according to clinical symptoms.
3. Treat with antibiotics, antivirals, and antifungals as needed.

4. If positive results are obtained in the sterility and endotoxin tests on culture test samples, administration should be discontinued immediately, and contaminated cells should be disposed of appropriately according to the waste disposal procedure. If the drug has already been administered, treat with antibiotics, antivirals, or antifungals as necessary.

## 10.5 Response to outbreaks of disease, etc.

### 10.5.1 Measures to be taken in case of outbreak of disease, etc.

#### *Reporting Procedure*

Based on the "Act on Securing Safety of Regenerative Medicine, etc.

#### **Principal Investigator**

Events and information that are judged to be serious by the Hiroshima University Regenerative Medicine Committee must be promptly reported to the Hiroshima University Hospital administration.

In addition, this clinical research may be discontinued or provisional measures may be taken, if necessary, before receiving instructions from the Hiroshima University Hospital administration.

#### **Head of the research institution**

1. When a serious situation is reported by a principal investigator, the occurrence and details of the situation shall be promptly reported to the Minister of Health, Labor and Welfare, the opinions of the Hiroshima University Regenerative Medicine Committee shall be promptly obtained on the policy for dealing with the situation, including analysis of the cause, and instructions shall be given to said principal investigator to stop the research or take other necessary measures. The committee shall promptly hear the opinion of the Hiroshima University Committee on Frontier Medical Sciences regarding the policy for dealing with the research, including the analysis of the research, and instruct the principal investigator of the research to stop the research or take other necessary measures. If necessary, the head of the research institution may instruct the person responsible for the research to suspend the research or to take temporary measures before hearing the opinion of the Hiroshima University Regenerative Medicine Committee.
2. The head of the research institution shall instruct the principal investigator to take the necessary measures listed in 1) above, and then report to the Minister of Health, Labor and Welfare the opinion of the Hiroshima University

Regenerative Medicine Committee, the results of the analysis of the cause, and the details of the measures instructed to the principal investigator.

3. 2), the results shall be reported to the Minister of Health, Labour and Welfare after discontinuation or other necessary measures have been taken.

#### 10.5.2 (Reporting of Diseases, etc. to the Accredited Committee for Regenerative Medicine, etc.)

In the event that any of the following events occurs, a report in accordance with Attachment Form 1 shall be submitted to the Accredited Committee for Rehabilitation Medicine, etc. on the relevant event within the period specified in each case.

(1) Outbreak of any of the following diseases, etc., which are suspected to be caused by the provision of said regenerative medicine, etc. or infectious diseases suspected to be caused by the provision of said regenerative medicine, etc.: 7 days

(a) Death

(a) Cases that may lead to death

(2) Outbreak of the following diseases, etc., which are suspected to be caused by the provision of said regenerative medicine, etc. or infectious diseases suspected to be caused by the provision of said regenerative medicine, etc.: 15 days

(a) Cases requiring hospitalization or extension of hospital stay at a medical institution for treatment

(a) Disability

(c) Cases that may lead to disability

(d) Cases that are serious (equivalent to a through c above)

(e) Congenital diseases or abnormalities in later generations

(3) Outbreak of disease, etc. caused by infectious diseases suspected to be caused by the provision of regenerative medicine, etc. or suspected to be caused by the provision of said regenerative medicine, etc. (excluding those listed in (1) and (2)) (3) Occurrence of diseases, etc. caused by infectious diseases suspected or alleged to be caused by the provision of regenerative medicine, etc. (excluding those listed in (1) and (2))

### 10.5.3 (Reporting of illness, etc. to the Minister of Health, Labor and Welfare)

In the event of the occurrence of any of the following matters, a report in accordance with Attachment Form 2 shall be submitted to the Minister of Health, Labor and Welfare on said matters within the period specified for each.

(1) Outbreak of any of the following diseases, etc., which are suspected to be caused by the provision of said regenerative medicine, etc. or infectious diseases suspected to be caused by the provision of said regenerative medicine, etc.: 7 days

(a) Death

(a) Cases that may lead to death

(2) Outbreak of any of the following diseases, etc., which are suspected to be caused by the provision of said regenerative medicine, etc. or infectious diseases suspected to be caused by the provision of said regenerative medicine, etc. 15 days

(a) Cases requiring admission to a medical institution for treatment or extension of hospital stay

(a) Disability

(c) Cases that may lead to disability

(d) Cases that are serious

(e) Subjects with congenital diseases or abnormalities in later generations.

#### *Reporting Procedure*

Based on the "Act on Securing Safety of Regenerative Medicine, etc.

#### *Principal Investigator*

Events and information that are judged to be serious by the Hiroshima University Regenerative Medicine Committee must be promptly reported to the Hiroshima University Hospital administration.

In addition, this clinical research may be discontinued or provisional measures may be taken, if necessary, before receiving instructions from the Hiroshima University Hospital administration.

#### *Head of the research institution*

4. When a serious situation is reported by a principal investigator, the occurrence and details of the situation shall be promptly reported to the Minister of Health, Labor and Welfare, the opinions of the Hiroshima University Regenerative Medicine Committee shall be promptly obtained on the policy for dealing with the situation, including analysis of the cause, and instructions shall be given to

said principal investigator to stop the research or take other necessary measures. The committee shall promptly hear the opinion of the Hiroshima University Committee on Frontier Medical Sciences regarding the policy for dealing with the research, including the analysis of the research, and instruct the principal investigator of the research to stop the research or take other necessary measures. If necessary, the head of the research institution may instruct the principal investigator to suspend the research or take other provisional measures before hearing the opinion of the Hiroshima University Regenerative Medicine Committee.

5. The head of the research institution shall instruct the principal investigator to take the necessary measures listed in 1) above, and then report to the Minister of Health, Labor and Welfare the opinion of the Hiroshima University Regenerative Medicine Committee, the results of the analysis of the cause, and the details of the measures instructed to the principal investigator.
6. 2), the results shall be reported to the Minister of Health, Labour and Welfare after discontinuation or other necessary measures have been taken.

## 11 Criteria and procedures for discontinuation of clinical research for each subject

### 11.1 Criteria for discontinuation of clinical research for each subject

The principal investigator or sub-investigator shall discontinue or suspend clinical research on the subject in the following cases

1. If a positive test is found in the infectious disease test of culture test material.
2. In addition to 1) above, if protocol treatment is no longer possible
3. When a subject requests withdrawal of consent for participation in clinical research.
4. When the occurrence of an adverse event is recognized and the principal investigator judges that it is difficult to continue the clinical research on the subject concerned.
5. If it is discovered after enrollment but before the start of protocol treatment that the subject did not meet the eligibility criteria
6. In other cases, when the principal investigator or sub-investigator deems it appropriate to discontinue the clinical research.

## 11.2 Procedures for discontinuing clinical research for each subject

The principal investigator shall promptly explain to the subject concerned that the clinical research is to be discontinued, and shall provide appropriate medical care and take other necessary measures. The reason for discontinuation and the date of discontinuation shall be stated in the case report form. If clinical research is discontinued after protocol treatment has been completed, observation and examination of the subject shall be continued as much as possible.

## 12 Compliance with the clinical research protocol and management of non-compliance

### 12.1 Compliance with the clinical research protocol

This clinical research will be conducted in compliance with this protocol, except in cases where it is medically unavoidable, such as to avoid urgent danger to subjects.

### 12.2 Management of non-conformities in the implementation plan

The principal investigator or sub-investigator may deviate from this protocol if there are unavoidable medical circumstances, such as the need to avoid immediate danger to subjects. In such cases, the principal investigator shall report the details of the deviation or change and the reason for the deviation or change to the Hiroshima University Regenerative Medicine Committee via the head of the research institution as soon as possible. In addition, the principal investigator or sub-investigator shall record all deviations from this protocol, regardless of the reason for the deviation.

If it is appropriate to change or revise the protocol, the draft shall be submitted to the Hiroshima University Regenerative Medicine Committee for approval via the head of the research institution. When changes are made, the ethical, scientific, and medical appropriateness of the changes will be thoroughly reviewed. The procedures for deviations and changes will be in accordance with the established procedures.

(2) When the rehabilitation medical care, etc. is found to be in a state that does not conform to the rehabilitation medical care provision plan, the fact shall be promptly reported to the administrator of the medical institution where the rehabilitation medical care, etc. is provided. In addition, when a particularly serious

non-conformity is found, the opinion of the authorized rehabilitation medical care commission shall be promptly heard.

## 13 Termination or discontinuation of the entire clinical study

### 13.1 Completion of clinical research

If the enrollment of the target cases is completed within the scheduled period, the date of the end of the observation period for the last enrolled case shall be the date of the end of the clinical research implementation period, and the following procedures shall be followed.

#### 13.1.1 Procedures for Termination of Research in Clinical Research

The principal investigator will report the completion of the clinical research implementation period to the chief statistician, the Hiroshima University Committee on Regenerative Medicine, the Hiroshima University Hospital administration, and relevant departments.

In addition, the principal investigator must prepare a summary report promptly after the completion of the clinical research and submit it to the administrator of Hiroshima University Hospital. In addition, the administrator of Hiroshima University Hospital must promptly submit a copy of the received summary report to the Minister of Health, Labor and Welfare.

### 13.2 Criteria and procedures for interruption or discontinuation of the entire clinical study

#### 13.2.1 Criteria for interruption or discontinuation of clinical research as a whole

The principal investigator will consider whether or not to continue the clinical research if any of the following applies

1. When significant information on the quality, safety, or efficacy of NK cell preparations is obtained
2. When it is judged difficult to complete the clinical research due to reasons such as delay in case enrollment or frequent deviation from the protocol.
3. If the safety of the protocol treatment is judged to be problematic based on the evaluation of the Hiroshima University Committee for Regenerative Medicine, etc.
4. If, as a result of evaluation of relevant information obtained from sources other than this clinical study, such as papers and conference presentations, it is

determined that there is a problem with the safety of the protocol treatment, or that the continuation of the clinical study is no longer meaningful.

### 13.2.2 Procedures for suspending or discontinuing the entire clinical study

The principal investigator shall promptly report to the Hiroshima University Regenerative Medicine Committee after discontinuing the clinical research.

In addition, the principal investigator must prepare a summary report promptly after discontinuation of the clinical research and submit it to the administrator of Hiroshima University Hospital. In addition, the administrator of Hiroshima University Hospital must promptly submit a copy of the received summary report to the Minister of Health, Labor and Welfare.

## 14 case report

### 14.1 data management

Data management will be outsourced to the Data Science Division (hereinafter referred to as "Data Center") of Hiroshima University Hospital's Center for Comprehensive Medical Care Research Promotion, in accordance with the Standard Operating Procedures for Clinical Research Quality Management (Monitoring and Data Management).

### 14.2 Case report writing and data collection

1. The principal investigator or sub-investigator shall prepare a case report form for each enrolled subject, submit it to the data center with his/her name, seal, or signature, and retain a copy of the report.
2. When research collaborators assist in the preparation of case report forms, they should only transcribe from the source documents to the extent that it does not involve medical judgment, under the supervision of the principal investigator or research subcontractor.

### 14.3 Notes on the Case Report Form

1. Use a black ballpoint pen or a pen with black ink.
2. The following is a summary of the results.
3. If no data is available due to lack of observation or inspection, put a shaded line (/) in the entry field.
4. Check for consistency with the source documents.

#### 14.4 Changes or modifications to the case report form

1. When changing or modifying a case report, cross out the changed or modified part with a double line (=), write the correct information near the changed or modified part, add the date of the change or modification, and seal or sign the document. Do not use correction fluid, sand eraser, etc. to obscure the original description.
2. In the case of changes or modifications to important information [consent, endpoint assessment (name of adverse event, date of occurrence, grade, severity, treatment, date of outcome/determination, causal relationship, comments)], the reason for the change or modification should be stated in addition to the date of the change or modification, and the change or modification should be stamped or signed.
3. Changes or corrections to the case report form after submission to the data center should be made via the DCF (Data Clarification Form) designated by the data center.

#### 14.5 Review of case reports

1. When a case report form is prepared by a research subcontractor, the principal investigator should inspect the contents of the case report form, confirm that there are no problems, and then write his/her name, seal, or signature on the form before submitting it to the data center.
2. Principal investigators will ensure that case report forms submitted to the data center are accurate, complete, legible, and submitted at the appropriate time, and that subject identification codes and registration numbers are used to identify subjects.

#### 14.6 Submission of case reports

The principal investigator, subcontractors, and research collaborators shall prepare a case report form, sign it with their names and seals, and submit it to the data center within six weeks after the completion of the final observation of each volume in the case or the discontinuation of clinical research, and keep a copy of the report.

## 15 Statistical Analysis

### 15.1 Statistical Analysis Method

As a rule, for items observed as continuous values, the number of examples, mean (median), standard deviation (quartiles), and range (minimum-maximum) are calculated as summary statistics. For items observed as discrete values, the number of examples in each category and their proportions are calculated as summary statistics.

Statistical tests for the main analysis will be performed at the 5% significance level (two-sided).

### 15.2 Definition of the population for analysis

#### 15.2.1 Efficacy analysis population

Subjects who are enrolled in this clinical study and underwent living partial liver transplantation and NK cells were administered on postoperative day 3 will be the target population for efficacy analysis (the largest analysis set Full Analysis Set: FAS).

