|                                                    | 
On the third day of culture, the cell suspension is centrifuged and washed with saline. Check the number of cells and viability after culture. At this time, the cell status, sterility test by Gram staining, endotoxin test, mycoplasma negative test, and bacterial culture test are performed. Suspend the cell suspension to be administered in albumin-containing saline.
 
4 . Cell shipment
The clinical research manager and the quality manager shall make the shipping judgment of the test article. For the infection test, the results of endotoxin test and bacterial culture test at the start of culture, as well as the results of cell condition and Gram stained sterility test method at the time of cell collection shall be used for the shipment judgment.
 
5 . Cell administration
On the third postoperative day after liver transplantation, with the permission of the recipient's primary physician, cell suspension is administered to the liver transplant recipient intravenously over a period of 30 minutes to 1 hour. The cells are administered only once, on the third postoperative day.
 |
| Concomitant use of prohibited drugs and therapies  | None in particular                                                                                                                                                                                                                                                                                                                                                                                                                                                                                                                                                                                                                                                                                                                                                                                                                                                                                                                                                                                                                                                                                                                                      |

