## 8 Primary and secondary endpoints

### 8.1 Primary endpoints

Incidence of bacteremia during the first month after surgery

Basis for setting primary endpoints

The onset of bacteremia, a severe infection after liver transplantation, is more likely to occur within one month after surgery (63%) based on the results of previous studies. Since the administered NK cells were confirmed in the recipient's body for up to one month, we chose one month as the period to evaluate the inhibition rate of bacteremia development by NK cell therapy.

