#### 15.2.2 Population for safety analysis

Subjects who are enrolled in this clinical study, underwent living partial liver transplantation, and received NK cells on postoperative day 3 will be the population for safety analysis.

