### 15.3 Handling of missing values

Withdrawals due to discontinuation or deviations during the course of the study will be reported to the

- ✓ The data observed immediately before the subject's discontinuation or dropout will be analyzed as the last observation data (Last Observation Carried Forward: LOCF).
- ✓ Analysis based on observed values without supplementing missing data (Observed Case: OC)
- ✓ Discontinuation and dropout cases will be analyzed as treatment failure cases (bacteremia cases/ Failure).

The robustness of the results of the analysis by the method of the primary endpoint will be confirmed. The primary endpoint will be analyzed as a failure (failure).

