## 15.5 Efficacy analysis

### 15.5.1 Primary endpoints

Incidence of bacteremia within 1 month after living donor liver transplantation  
[Main analysis]

The incidence of bacteremia within 1 month after living donor liver transplantation and its 95% confidence interval will be calculated for FAS. In addition, the following statistical hypothesis test will be performed at a significance level of 5% (two-tailed) by chi-square test using the 30% incidence of bacteremia with non-NK therapy observed in previous studies as a threshold.

The null hypothesis: "The incidence of bacteremia  $p$  in NK therapy is equal to a threshold of 30% ( $p = 0.3$ )."

Counter-hypothesis: "The incidence of bacteremia  $p$  in NK therapy is less than the threshold of 30% ( $p < 0.3$ )"

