### 15.5.2 Secondary endpoints

#### ① Overall survival time

FAS will be observed from the date of surgery to the date of death (regardless of the cause of death) or the date of confirmed survival, and the survival curve for overall survival will be estimated using the Kaplan-Meier method, and the median overall survival and its 95% confidence interval will be calculated. The median overall survival and its 95% confidence interval will be calculated. The survival rates at 6 months, 1 year and 3 years and its 95% confidence interval will be calculated. The Greenwood method will be used to calculate the confidence intervals.

- ② Effect on immune response (evaluation of donor-specific immune responsiveness by CFSE-MLR, detection of DSA, incidence of rejection, evaluation of NK cell activity in recipient peripheral blood).  
For CFSE-MLR and evaluation of recipient peripheral blood NK cell activity for FAS, summary statistics and changes from baseline (mean (median), standard deviation (quartiles)) and their 95% confidence intervals will be calculated for each observation time point. For detection of DSA and incidence of rejection, the number of cases in each category and its percentage will be calculated.
- ③ Hepatocellular carcinoma recurrence / De novo carcinogenesis  
We will observe whether hepatocellular carcinoma (HCC) recurs in FAS and the date of recurrence, and calculate the HCC recurrence rate and its 95% confidence interval, and the mean time to recurrence and its 95% confidence interval. De novo carcinogenesis will be analyzed in the same way.
- ④ Incidence of infectious diseases  
The percentage of subjects who developed bacterial, cytomegalovirus, and fungal infections and their 95% confidence intervals will be calculated. The incidence of infectious diseases by genetic polymorphism will be calculated, and comparisons between genetic polymorphisms will be made using Fisher's direct probability method at a significance level of 5% (two-sided).

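### The efficacy set admits only recipients infused on postoperative day 3 while bacteremia is counted from surgery, so the tested rate can be biased low if failure to infuse is related to infection

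*Protocol*

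**What the plan says.** The primary endpoint in protocol section 8.1 is "Incidence of bacteremia during the first month after surgery". Section 15.5.1 repeats the window and names the set: "The incidence of bacteremia within 1 month after living donor liver transplantation and its 95% confidence interval will be calculated for FAS". The null hypothesis there is "The incidence of bacteremia $p$ in NK therapy is equal to a threshold of 30" per cent.

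Section 15.2.1 limits that set to enrolled subjects who "underwent living partial liver transplantation and NK cells were administered on postoperative day 3 will be the target population for efficacy analysis". Section 15.2.2 applies the same limit to safety: those who "received NK cells on postoperative day 3 will be the population for safety analysis".

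Enrolment comes first. Under section 5.1, item 4, collection of the cells and the transplantation begin only after enrolment has been confirmed. Between enrolment and infusion there are several ways to drop out of the set:

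- The Overview allows infusion only "with the permission of the recipient's primary physician".
- Section 6.2.1 sets release standards for the product.
- Section 11.1 discontinues a subject if the product tests positive (item 1) or if treatment cannot be given (item 2).
- A recipient may die before day 3.

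Section 15.3 contains the rule "Discontinuation and dropout cases will be analyzed as treatment failure cases", counted as bacteremia.

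**The concern.** The set is labelled a full analysis set, but it is an as-treated set. Entry depends on something that happens three days into a one-month window and that an unblinded physician can influence. Bacteremia on day 1 or 2 counts as an event if the recipient is later infused and is lost if not. No criterion in the protocol says which of the two follows.

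The rule in 15.3 looks like protection, but a recipient discontinued before infusion has never entered the set to which it applies. For these recipients 15.2.1 and 15.3 do not fit together.

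The information may also be lost for good. Section 11.2 asks for continued observation only when discontinuation follows completed protocol treatment, and section 9.2.11 collects only a reason and a comment.

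At stake is the trial's single confirmatory test. If infection or instability is a reason not to infuse, the tested rate is lower than the rate among all who were transplanted.

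**Working it through.** **Inputs.** Threshold 30%, expected rate 10%, two-sided 5%, power 80%, 34 needed and 37 enrolled (7.2); chi-square test against 30% (15.5.1). The protocol does not give the share not infused (w) or the bacteremia rate among them (q). Both are varied below as assumptions.

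**1. The plan's own figure.** n = [(1.960·√(0.3·0.7) + 0.842·√(0.1·0.9)) / 0.2]² = 33.1, rounded up to 34. This agrees with the protocol. Going from 34 to 37 allows a loss of 3/37 = 8.1%.

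**2. Limits for success.** With z = (x/n − 0.30)/√(0.21/n) and success at z ≤ −1.96, the largest successful count is 4 for n = 34 and 5 for n = 37.

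**3. Rate in the infused set.** Suppose NK therapy does nothing and the true rate in all transplanted recipients is 30%. The rate in the infused set is then (0.30 − w·q)/(1 − w). For w = 6% and q = 1 this is 0.24/0.94 = 25.5%. False success is the exact binomial probability of a count at or below the limit, averaged over the number infused out of 37.

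| w | q | Rate in infused set | False success |
|---|---|---|---|
| 3% | 0.3 | 30.0% | 2.0% |
| 3% | 0.5 | 29.4% | 2.5% |
| 3% | 1.0 | 27.8% | 3.8% |
| 6% | 0.3 | 30.0% | 2.0% |
| 6% | 0.5 | 28.7% | 2.9% |
| 6% | 1.0 | 25.5% | 6.6% |

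Analysing all 37 gives 1.7%. Part of the gap to 1.7% is not bias: at q = 0.3 the rate is unchanged and false success is still 2.0%, because the limit moves in whole events (at n = 35, five or fewer has probability 2.7%). The nominal lower tail is 2.5%. With w = 6% and q = 0.1 the rate moves the other way, to (0.30 − 0.006)/0.94 = 31.3%.

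**4. A single trial.** Take 3 of 37 not infused, equal to the protocol's dropout allowance, and 4/34 = 11.8% in the infused set (p = 0.020).

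| Bacteremia among the 3 | All 37 | p |
|---|---|---|
| 0 | 4/37 = 10.8% | 0.011 |
| 1 | 5/37 = 13.5% | 0.029 |
| 2 | 6/37 = 16.2% | 0.067 |
| 3 | 7/37 = 18.9% | 0.14 |

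The result is lost at two or more.

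**5. Power.** With 34 infused at a 10% rate, the chance of 4 or fewer events is 75%. Adding 3 non-infused and allowing 5 or fewer of 37 gives 84%, 75%, 64% or 33% at q = 0.1, 0.3, 0.5 or 1.0.

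**The case against.** A reader might infer that early infections leave the numerator and that the rate is therefore biased low. The documents do not support that. The set excludes for lack of infusion, not for infection; no criterion bars infusing a recipient with bacteremia, and one who is infused counts as an event. Those not infused leave the denominator too, so the rate falls only if they have more bacteremia than the infused. A technical product failure need not be related to infection.

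A reader might also infer that a selected group is being compared with an unselected one. Sections 2.2.3 and 7.2 describe 21 propensity-matched controls from a series of 114. They mention no day-3 landmark and do not rule one out. If there was one, the comparison is closer to like with like.

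The rationale for the design under 7.1 speaks of incidence during NK therapy in a Phase I/II study, so an infused set answers a legitimate question. Section 15.4 tabulates discontinuations by period and reason, so losses would be partly visible. Infusion on another day would be a deviation, so the gap in the safety set should be small.

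These points limit the size and certainty of the bias. They leave the main defect in place: set and endpoint start at different times, the failure rule cannot reach pre-infusion losses, and no output gives the bacteremia status of those recipients.

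**Conclusion.** The point stands in a conditional form. The main set is conditioned on an event inside the endpoint window, and the tested rate can be biased low if non-infusion is related to infection or instability. The direction is plausible but not established.

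The size rests on assumed values of w and q. With 3% to 6% not infused, the effect on the rate runs from nothing at q = 0.3 to 4.5 points at q = 1 and w = 6% (30.0% to 25.5%), and false success from 2.0% to 6.6%. The upper end requires every excluded recipient to have had bacteremia. With three recipients lost, two events among them are enough to reverse a success at 4/34.

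Overall survival is also affected, since "FAS will be observed from the date of surgery to the date of death" while membership guarantees survival to day 3. For estimates at 6 months, 1 year and 3 years this is minor.

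**What to change.** - Make the main-analysis set all enrolled recipients who underwent the transplantation, infused or not. Count bacteremia from surgery for one month, and handle pre-infusion discontinuations as 15.3 states.
- Record one-month bacteremia status and the reason for every recipient not infused.
- Keep the infused set as a supportive analysis, counted from infusion in recipients free of bacteremia at that time.
- Define the safety set as every recipient who received any NK cells.

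The cost is protocol wording, a few extra chart reviews and possibly a less favourable estimate. The effect on power depends on q. With 3 of 37 not infused it is about the same as for 34 infused at q = 0.3 (75% in both) but falls to 64% at q = 0.5. If the failure rule is applied literally to every non-infused recipient, q is in effect 1 and power is 33%. The recorded status then lets the observed-case analysis, also listed in 15.3, be shown beside it. This is a cheap improvement, best made before any recipient's status is lost.
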